#### Costs

2.7.9

Both direct healthcare costs and indirect costs will be collected. Direct healthcare costs will include epilepsy‐related clinic visits, visits to the general practitioner or other specialists, and emergency department presentations; use of chronic disease services; allied health services; and hospitalizations. Data linkage from the Medicare Benefits Scheme and Pharmaceutical Benefits Scheme will be utilized. The study dietitians will record the mode (e.g., in‐person, video call, phone or email), time (min) of encounters with trial participants of scheduled and unscheduled contact. Indirect healthcare costs will be collected using out‐of‐pocket costs and informal care questionnaires at Visits 2, 7, 8, 9, and 10.

Utilizing the quality‐of‐life measures (EQ‐5D‐5L for adults), a preference‐based scoring algorithm will be used to generate scores (0 = dead, 1 = full health scale) for economic evaluation. Indirect costs will be measured in terms of productivity loss due to seizure‐related absence from work or days of inactivity using the Work Productivity and Activity Impairment‐General Health^21^ at randomization (Week 0), at the completion of the treatment (Week 14), and at each 12‐week follow‐up visit (Weeks 26, 36, and 50).

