### Study design

2.3

This is a two‐arm, randomized, controlled trial (Figure 1). The trial will be based at the Alfred Hospital in Melbourne, Australia. All study assessments can be completed at in‐person or by telemedicine visits ±7 days from the scheduled visit date. The number and timing of study visits will be the same in both treatment groups. A total of 136 participants will be recruited over 3 years.

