#### ET intervention 3: Dynamic dietitian support

2.6.6

The dietitian will have access to dietary intake information, seizure records, and saliva ketone levels prior to each study visit. This is in contrast to the standard care group, where this information is provided during the study visit, where participants provide a summary of their paper‐based seizure diaries and urine ketone testing results during the consultation. The dietitian will review the digital information prior to the study visit and provide individualized advice for the review consultations to further optimize dietary treatment. For example, if a participant had no change in seizure frequency and low saliva BHB concentration, dietary advice on further reduction in carbohydrate and increasing fat intake would be provided. Similarly, advice on management of side effects could be provided, such as increasing fiber and fluid intake to manage constipation. Early interventions to mitigate side effects may improve adherence and retention on dietary therapy.

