### Study assessments

2.7

All study outcome assessments will be conducted by an outcome assessor, blinded to the participant group allocation (Table 3).

**TABLE 3 epi470345-tbl-0003:** Schedule of study assessments.

Assessment/procedure	Screening	Run‐in phase	Start of treatment phase	Treatment phase			End of trial	Follow‐up phase		
	Visit 1 (Week 2)	Visit 2 (Week 0)	Visit 3 (Week 2)	Visit 4 (Week 4)	Visit 5 (Week 6)	Visit 6 (Week 10)	Visit 7 (Week 14)	Visit 8 (Week 26)	Visit 9 (Week 36)	Visit 10 (Week 50)
Informed consent	x									
Assess eligibility	x									
Confirm eligibility		x								
Demographic information	x									
Medical and epilepsy history	x									
Dietitian session	x	x	x	x	x	x	x	x	x	x
Food diary	x	x	x	x	x	x	x	x	x	x
Pathology	x						x	x	x	x
Plasma HCG	x									
Dispense study diaries Seizure record Food record Adverse events Medication use	x	x	x	x	x	x	x	x	x	x
Randomization	x									
Dispense urine Keto‐Diastix (standard group only)	x				x			x (all participants)	x (all participants)	
Dispense MX3 Lab Device and consumables (intervention group only)	x				x		x			
QOLIE‐31	x						x	x	x	x
EQ‐5D‐5L	x						x	x	x	x
CES (if applicable)	x						x	x	x	x
WPAI	x						x	x	x	x
Out of pocket costs and Informal care Questionnaires	x						x	x	x	x
Review of AEs/SAEs	x		x	x	x	x	x	x	x	x
Gastrointestinal symptoms questionnaire	x						x	x	x	x
Evaluation questionnaires							x			

Abbreviations: β‐hCG, beta‐human chorionic gonadotrophin; AE, adverse event; CES, Carer Experience Scale; EQ‐5D‐5L, EuroQol Five‐Dimensional Five‐Level; QOLIE‐31, Quality of Life in Epilepsy Inventory‐31; SAE, serious adverse event; WPAI, work productivity and activity impairment‐general health.

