### Secondary end points

3.3

*Seizures*: Proportion of participants with ≥50% and 100% (seizure‐free) reduction in seizure frequency per 28 days after 12 weeks dietary therapy will be compared between groups.
*Retention on dietary therapy*: Proportion of participants remaining on the MKD after 12 weeks of treatment will be compared between groups.
*Adverse events related to dietary therapy*: The total number and severity of adverse events will be compared between groups after 12 weeks of treatment.
*Psychiatric symptoms and QOL*: The proportion of participants experiencing a clinically meaningful improvement in psychiatric symptoms and QOL questionnaire scores will be compared between groups after 12 weeks of treatment.
*Regular and rescue medication use*: Change in the number of regular medications and instances of rescue medication use will be compared between groups after 12 weeks of treatment.
*Cost‐effectiveness evaluation*: Direct and indirect healthcare costs and loss of productivity will be compared between groups after 12 weeks of treatment.
*Acceptance of technology‐assisted healthcare delivery*: The Theoretical Framework of Acceptability (TFA) questionnaire^20^ will be used to assess the acceptability of ketogenic diet therapy and the ET intervention by participants.

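### The dietitian time log covers participant contact, so the pre-visit data review that defines ET support is missed while the standard-care counterpart is counted

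*Protocol article*

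**What the plan says.** Section 2.7.9 (Costs) sets out what is collected for the economic comparison. The study dietitians record the mode of contact (the examples are in-person, video call, phone and email) and the "time (min) of encounters with trial participants of scheduled and unscheduled contact". No record of time spent without the participant is described.

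Section 2.6.6 (ET intervention 3) places the ET-specific dietitian work before the visit: "The dietitian will review the digital information prior to the study visit and provide individualized advice". It then sets the arms against each other: "This is in contrast to the standard care group, where this information is provided during the study visit". Section 2.6.2 agrees, since standard-care advice rests on what is gathered in the consultation.

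Section 2.3 (Study design) holds the schedule equal: "The number and timing of study visits will be the same in both treatment groups". Section 3.3 makes the comparison a secondary endpoint: "Direct and indirect healthcare costs and loss of productivity will be compared between groups after 12 weeks of treatment".

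**The concern.** The same task, taking in the participant's diet, seizure and ketone information, sits inside the recorded encounter in one arm and outside it in the other. The measurement error therefore differs by arm, and it falls on the activity that distinguishes ET dietitian support from standard care.

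The endpoint at stake is the between-group cost comparison. If dietitian minutes are costed from this log, ET delivery is charged for its contact time alone, while standard care is charged for contact time that already contains the information gathering.

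The timing of the correction matters. A health-economic plan can later choose prices and perspective, but it cannot supply resource use that nobody recorded.

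**Working it through.** The document states no review time, unit price or incremental cost, so there is no figure of its own to reproduce. The check is a comparison of sections, followed by an illustration of size.

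**Step 1: where the work falls in each arm.**

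| | ET | Standard care |
|---|---|---|
| When the information reaches the dietitian | Before the visit (2.6.6) | During the visit (2.6.2, 2.6.6) |
| Inside the encounter minutes of 2.7.9? | No, on a plain reading | Yes |

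**Step 2: direction.** Write C for contact minutes and R for non-contact review minutes per participant, with subscripts E (ET) and S (standard care).

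- True difference in dietitian time: D = (C_E + R_E) − (C_S + R_S).
- Logged difference: D_log = C_E − C_S.
- Error: D_log − D = −(R_E − R_S).

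Section 2.6.6 describes review before the visit for ET and contrasts it with standard care, so R_E exceeds R_S as the interventions are described. The logged difference is then too low by R_E − R_S, which favours ET. This holds whether or not ET consultations turn out shorter.

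**Step 3: could another described source recover R_E?** Visit counts cannot, because the schedule is the same in both arms. The Medicare and pharmaceutical benefits linkage and the participant questionnaires would not be expected to record a study dietitian's preparation time.

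**Step 4: size under an assumption.** Inputs: five dietitian visits in the treatment phase (Visits 3 to 7, section 2.3 and Table 3); review time per visit r = 5 to 30 minutes (assumed, not in the document); R_S taken as 0.

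- Per ET participant completing all five visits: 5 × 5 = 25 minutes to 5 × 30 = 150 minutes.
- If Visit 2 also involves such a review: 6 × 5 = 30 to 6 × 30 = 180 minutes.
- Across the arm with all 136/2 = 68 completing: 68 × 25/60 = 28 hours to 68 × 150/60 = 170 hours. This is a ceiling.
- With the 108 participants of the power calculation, 108/2 = 54 per arm: 54 × 25/60 = 22.5 hours to 54 × 150/60 = 135 hours, and less if more participants stop early.

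**The case against.** The strongest reply is that section 2.7.9 says what is recorded and does not exclude preparation. The listed modes include email, so logged time is not confined to live consultation. A full protocol or case report form could define a scheduled encounter's minutes to include preparation, and a journal article need not reproduce that definition. This has some force: the finding rests on a plain reading of the log rule. But the rule is stated, it is tied to encounters with participants, and every listed mode is participant contact. If preparation is meant to be included, saying so costs nothing.

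A second reply is that a standard-care participant's summary of paper records is not the same as a full digital review, and that nothing says ET consultations will be shorter. That stands. A reader might infer that ET will appear to save dietitian time; the documents do not support going that far. The error in Step 2 does not depend on it.

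A reader might also infer that the device and its consumables go uncounted, since the direct-cost list, which ends with "use of chronic disease services; allied health services; and hospitalizations", names neither. The documents do not support that. The list is not stated to be exhaustive. Table 3 schedules the dispensing ("Dispense MX3 Lab Device and consumables (intervention group only"), so quantities can be taken from dispensing records and priced later. The urine strips ("standard group only" until follow-up) are equally unlisted, so any effect would be a net difference that the document does not price.

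Nor can the unlogged review be called most of the arm difference in delivery cost. Equal visit schedules fix neither visit length nor unscheduled contact, and both of those are logged.

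**Conclusion.** The concern holds for dietitian time. Followed as written, the log under-records ET dietitian time relative to standard care, in a direction that favours ET in the secondary cost comparison. This rests on two readings: that encounter minutes mean time in contact with the participant, and that the pre-visit review takes place as section 2.6.6 describes.

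The size cannot be derived from the document. The 25 to 150 minutes per completing ET participant depends entirely on the assumed 5 to 30 minutes per visit, and the weight of those minutes in total cost is unknown because healthcare use and productivity also enter the endpoint. The primary endpoint, the sample size and the safety assessments are unaffected. It is worth correcting because the remedy is small and works only while data are being collected.

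**What to change.** Amend section 2.7.9 so that the dietitians log participant-related non-contact time (pre-visit data review and preparation) in a field separate from contact time, in both arms, from now on. Using the field in both arms keeps the measure symmetric and captures any preparation done for standard-care participants. Keeping it separate allows contact-only and total dietitian time to be reported side by side. For any participants treated before the change, treat their non-contact minutes as missing, not as zero.

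The cost is one extra field on an existing log, slightly more recording work for the dietitians, and a possibly less favourable cost result for ET.

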### Monitoring and data quality

2.8

An independent clinical trial monitor will conduct onsite monitoring. Onsite monitoring will ensure adherence to the study protocol and procedures from both a patient safety and data quality aspect. The frequency of the monitoring will be determined by the rate of participant recruitment, with the first monitoring visit occurring after the first three participants have completed the 12‐week treatment phase, and then after every 30 participants have completed the 12‐week treatment phase. A total of 27 participants (20% of all participants) will be audited for safety and data quality. A final monitoring visit will occur after the final participant has completed their last study assessment and prior to data lock. The clinical trials monitor will provide a report at the end of each monitoring visit. These reports will be reviewed at the quarterly steering committee meetings.

## ENDPOINTS AND STATISTICAL ANALYSIS OVERVIEW

3

### Power and sample size

3.1

Power analysis for the win ratio outcome requires the alternative hypothesis about the combination of proportions of all one‐to‐one comparisons to a random participant in the standard care arm, where a random participant receiving the ET intervention will have a better, worse, or same epilepsy‐DOOR scale outcome, respectively (proportions of wins, losses, and ties). We hypothesize that the ET intervention will result in a distribution of win/draw/loss proportions of 0.6:0.1:0.3 that corresponds to the Win ratio = 0.6/0.3 = 2 accounting for potential ties.

Recruiting 108 participants would provide a power of 0.8 to detect the hypothesized treatment effect, testing against the null hypothesis of no treatment effect (Win ratio = 1), assuming a two‐sided alpha level of 0.0533. The final sample size is set at 136 participants distributed between intervention and control, accounting for 20% potential losses due to screening failures and participant withdrawal from the study.

### Primary end point

3.2

The odds that a random participant who received ketogenic diet therapy with the addition of the ET intervention will have a more desirable epilepsy‐DOOR scale outcome than a random participant who received ketogenic diet therapy as per standard care at 12 weeks from the start of the intervention.

### Secondary end points

3.3

*Seizures*: Proportion of participants with ≥50% and 100% (seizure‐free) reduction in seizure frequency per 28 days after 12 weeks dietary therapy will be compared between groups.
*Retention on dietary therapy*: Proportion of participants remaining on the MKD after 12 weeks of treatment will be compared between groups.
*Adverse events related to dietary therapy*: The total number and severity of adverse events will be compared between groups after 12 weeks of treatment.
*Psychiatric symptoms and QOL*: The proportion of participants experiencing a clinically meaningful improvement in psychiatric symptoms and QOL questionnaire scores will be compared between groups after 12 weeks of treatment.
*Regular and rescue medication use*: Change in the number of regular medications and instances of rescue medication use will be compared between groups after 12 weeks of treatment.
*Cost‐effectiveness evaluation*: Direct and indirect healthcare costs and loss of productivity will be compared between groups after 12 weeks of treatment.
*Acceptance of technology‐assisted healthcare delivery*: The Theoretical Framework of Acceptability (TFA) questionnaire^20^ will be used to assess the acceptability of ketogenic diet therapy and the ET intervention by participants.

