### Aims

1.1

The primary aim of this study is to investigate if 12 weeks of ketogenic diet therapy with multimodality enhanced technology (ET) support improves clinical outcomes in people with drug‐resistant epilepsy compared to standard‐of‐care ketogenic diet therapy alone. Improvement of clinical outcome will be defined using the epilepsy desirability of outcome rank (e‐DOOR) ordinal scale which has been co‐designed with people with drug‐resistant epilepsy.^12^

Secondary aims of the study relate to changes in seizure frequency, retention on ketogenic diet therapy, adverse events related to dietary therapy, quality of life, medication use, and direct and indirect healthcare costs. Acceptability of ketogenic diet therapy and the digital health intervention by participants will also be assessed.

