#### Psychiatric symptoms

2.7.6

The Neurological Disorders Depression Inventory in Epilepsy (NDDI‐E)^15^ and Brief Epilepsy Anxiety Survey Instrument (BrEASI)^16^ questionnaires will be completed at baseline (Week −2), at the completion of the treatment period (Week 14), and at each 12‐week follow‐up visit (Weeks 26, 36, and 50).

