#### Quality of life (QOL)

2.7.7

Questionnaires will be completed at baseline (Week 2), at the completion of the treatment (Week 14) at each 12‐week follow‐up visit (Weeks 26, 36, and 50). Health‐related QOL will be measured by both generic and epilepsy‐specific instruments. The EuroQol Five‐Dimensional Five‐Level (EQ‐5D‐5L)^17^ and Quality of Life in Epilepsy Inventory‐31 (QOLIE‐31)^18^ will be completed by the participant or proxy. Carer QOL will be measured by the Carer Experience Scale.^19^

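### Psychiatric and quality-of-life scores are compared between groups only as proportions improved, which gives up power that a baseline-adjusted score comparison would keep; Table 3 also omits the two psychiatric scales

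*Protocol article*

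**What the plan says.** Section 3.3 (Secondary end points) sets the comparison for psychiatric symptoms and quality of life after 12 weeks of treatment: "The proportion of participants experiencing a clinically meaningful improvement in psychiatric symptoms and QOL questionnaire scores will be compared between groups". It names no mean, change-score or baseline-adjusted comparison and gives no threshold for a meaningful improvement.

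The scores themselves are available. Under section 2.7.6, NDDI-E and BrEASI "questionnaires will be completed at baseline" (Week -2), at Week 14 and at Weeks 26, 36 and 50. Section 2.7.7 states that "Health‐related QOL will be measured by both generic and epilepsy‐specific instruments", namely EQ-5D-5L and QOLIE-31, at baseline, Week 14 and the same follow-up visits.

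Table 3, captioned "Schedule of study assessments", has rows for QOLIE-31, EQ-5D-5L, the carer scale, WPAI, the cost questionnaires, the "Gastrointestinal symptoms questionnaire" and the evaluation questionnaires. It has no row for NDDI-E or BrEASI, and neither appears in its abbreviation list.

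Section 3.4 leaves full analysis details to a statistical analysis plan, which is not at hand.

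**The concern.** A participant who improves by just more than the cut counts the same as one who improves by three times as much. One who just misses it counts the same as one who gets worse. The baseline score enters only through the subtraction that decides on which side of the cut a person falls, so its value as a covariate that removes between-person variation is not used.

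The trial is modest in size, and its stated power concerns the primary win-ratio endpoint only. If the group comparison of these scores rests on proportions alone, an effect of moderate size could easily be missed with data that could have shown it.

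The gap in Table 3 is a separate matter of consistency. Psychiatric symptoms are a declared secondary outcome, and an improvement endpoint cannot be rebuilt later if a baseline score was missed, so the text and the table should agree.

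**Working it through.** **1. Number per arm.** Section 3.1 gives a win/draw/loss split of 0.6:0.1:0.3, a win ratio of 2, power 0.8, 108 participants, and 136 after allowing for 20% losses. The usual win-ratio formula is N = s²(z₁₋α/₂ + z₁₋β)² / (ln WR)², with s² = 4(1 + p_tie) / [3k(1 − k)(1 − p_tie)]. With k = 0.5 and p_tie = 0.1, s² = 4.4/0.675 = 6.52. At α = 0.05, N = 6.52 × 7.85 / 0.480 ≈ 106.5, which is 108 as an even total. At the printed α of 0.0533, N ≈ 104.4. The plan's 108 is therefore reproduced, and 108/0.8 = 135, or 136 for equal arms. The evaluable number is 54 per arm, and it is the right one to use here because 136 already includes the allowance for losses.

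**2. Inputs that the article does not give (assumptions).** Scores are normal with SD 1; the true difference d is 0.4 to 0.5 SD; the baseline to Week 14 correlation r is 0.3 to 0.8; the cut for improvement c is 0.3 to 0.5 SD; the control-arm mean improvement m is 0 to 0.2 SD; the test is two-sided at 0.05; Week 14 scores are complete for all 54 per arm.

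**3. Baseline-adjusted mean.** Power = Φ(d / [√(1 − r²)·√(2/n)] − 1.96). With d = 0.4, r = 0.6, n = 54: residual SD = √0.64 = 0.80; standard error = 0.80 × 0.1925 = 0.154; 0.4/0.154 = 2.60; Φ(0.64) = **0.74**.

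**4. Proportion improved.** The SD of change is √[2(1 − r)] = 0.894. With c = 0.5 and m = 0.2:
- control: 1 − Φ(0.3/0.894) = 0.369
- intervention: 1 − Φ(−0.1/0.894) = 0.544

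The difference is 0.176. The pooled standard error is 0.0959 and the unpooled one 0.0944. Power = Φ([0.176 − 1.96 × 0.0959]/0.0944) = Φ(−0.13) = **0.45**.

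**5. Where the loss arises.** An unadjusted comparison of mean change has power Φ(0.4/[0.894 × 0.1925] − 1.96) = Φ(0.36) = 0.64. In this example the step from 0.74 to 0.64 comes from not using baseline as a covariate, and the step from 0.64 to 0.45 from dichotomising.

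**6. Range at 54 per arm.** Proportion ranges cover the values of c and m above.

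| d (SD) | r | Proportion improved | Baseline-adjusted mean | Loss (points) |
|---|---|---|---|---|
| 0.4 | 0.3 | 28% | 59% | 31 |
| 0.4 | 0.5 | 37% | 67% | 30 |
| 0.4 | 0.7 | 54–56% | 83% | 27–29 |
| 0.4 | 0.8 | 70–73% | 93% | 20–23 |
| 0.5 | 0.3 | 41% | 78% | 37 |
| 0.5 | 0.5 | 53–54% | 85% | 31–32 |
| 0.5 | 0.7 | 74–76% | 95% | 19–21 |
| 0.5 | 0.8 | 88–90% | 99% | 9–11 |

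For 80% power the proportion needs about 1.8 to 2.5 times as many participants. With all 68 per arm in the example of steps 3 and 4, the figures would be 0.54 and 0.83, so the gap does not depend on the choice of 54.

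**7. Text against table.** Section 2.7.6 gives Weeks -2, 14, 26, 36 and 50 for both psychiatric scales. These are Visits 1, 7, 8, 9 and 10 in Table 3, where QOLIE-31 and EQ-5D-5L are marked and the psychiatric scales are not listed.

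**The case against.** A responder endpoint built on clinically meaningful change is legitimate and easy to interpret. These are secondary endpoints for which no power is claimed, model details are deferred to the analysis plan, and every input to the power figures is assumed. All of that is true. It supports keeping the proportion and reading the figures as illustrations. It does not remove the point: the article has already named the summary measure, a covariate-adjusted responder model would still analyse the dichotomised score, and the loss was material under every assumption tried.

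A reader might infer more than the documents support:

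- *Baseline scores are thrown away.* They are not, since improvement is measured from baseline. What is lost is the size of the change and efficient adjustment.
- *The quality-of-life data have no other use.* Section 2.7.9 also turns EQ-5D-5L into preference-based scores for the economic evaluation, and quality of life enters the primary e-DOOR at three levels.
- *Seizure frequency is analysed only as responder proportions, against the aim.* Section 1.1 says "Secondary aims of the study relate to changes in seizure frequency", and section 3.3 does use the 50% and 100% thresholds, but the primary e-DOOR also ranks four levels of seizure reduction. Percent reduction from baseline is a change in frequency, so aim and endpoint do not conflict.
- *The psychiatric scales would not be collected.* Section 2.7.6 names both scales and all five time points, the trial is based at one hospital, and nothing shows that staff work from the article's table.
- *A null result would say nothing.* A confidence interval for a difference in proportions still informs; it is only less precise than it need be.

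Low baseline symptom scores could dilute the proportion further, because eligibility does not require psychiatric symptoms. No baseline distribution is given, so that effect was not quantified and carries no weight here.

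**Conclusion.** The point holds in a limited form. The only between-group comparison that section 3.3 names for the psychiatric and quality-of-life scores is a proportion improved, and a baseline-adjusted comparison of the same data would be clearly more powerful. The example gives about 0.45 against 0.74 at 54 per arm, and the loss over the range examined is roughly 9 to 37 percentage points. The direction is stable; the size rests on an assumed effect, correlation, cut-off and control improvement, on normality, and on complete Week 14 scores. This is a worthwhile improvement to secondary analyses. It is not an error in the trial's main inference.

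The mismatch between Table 3 and section 2.7.6 needs no assumption. It is an inconsistency to reconcile, and it does not show that data will be missed.

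**What to change.** For NDDI-E, BrEASI, QOLIE-31 and EQ-5D-5L, add a between-group comparison of the Week 14 score, adjusted for its baseline value and the two stratification factors (baseline seizure frequency and need for a decision maker or caregiver). Report the adjusted mean difference with its confidence interval and the proportion improved beside it.

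The cost is a few extra models and some wording in the analysis plan; no new data are needed. The added analysis does need a stated way of handling missing Week 14 scores, including those of participants who stop the diet.

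Separately, reconcile Table 3 with section 2.7.6 so that both show the same time points for NDDI-E and BrEASI. That is two table rows and two abbreviations.

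A model of seizure counts is optional. If one is added, its baseline covariate must be defined for a participant with no seizures in the 2-week diary baseline, because eligibility requires two seizures only in the 28 days before enrolment and the logarithm of a zero rate does not exist.

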### Patient and public involvement statement

2.4

The study protocol was prepared in consultation and co‐designed with consumers. This process involved formation of a Consumer Advisory Committee which includes authors [name]. The Consumer Advisory Committee members are people with lived experience of epilepsy and/or are representatives of the epilepsy advocacy agencies, Australian Women with Epilepsy, Epilepsy Foundation and Epilepsy Action Australia. The Consumer Advisory Committee has reviewed and approved the study protocol and study‐associated participant materials.

The primary outcome of the study is a novel consumer codesigned e‐DOOR specific for use in clinical trials in epilepsy. Details of the development of the e‐DOOR have been published elsewhere.^12^ In brief, the e‐DOOR is a composite outcome measure combining four levels of reduction in seizure frequency, five levels of adverse events, and three levels of quality of life, resulting in 60 combinations of potential outcomes, which are ranked from most desirable to least desirable (Table 2).

**TABLE 2 epi470345-tbl-0002:** Epilepsy desirability of outcome rank (e‐DOOR) (adapted from Vivash et al.^12^).

Outcome	Seizure frequency	Adverse events (AE)	Quality of life	Outcome rank
Levels	>90% reduction	No AE	Improvement	>90% reduction in seizure frequency, no AE and improvement in quality of life
	>50% reduction	Mild temporary AE	No change	2 >90% reduction in seizure frequency, no AE and no change in quality of life
	>25% reduction	Mild ongoing AE	Worsening	30. >90% reduction in seizure frequency, moderate ongoing AE, and worsening of quality of life
	<25% reduction	Moderate ongoing AE		59. <25% reduction in seizure frequency, severe ongoing AE, and no change in quality of life
		Severe ongoing AE		60. <25% reduction in seizure frequency, severe ongoing AE, and worsening in quality of life

Abbreviation: AE, Adverse events.

The results of the study will be presented at national and international scientific meetings and published in peer‐reviewed journals. In collaboration with the consumer advisory committee, the results will be publicized to the wider community.

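### Section 3.3 compares quality of life and mood scores between arms only as an improvement proportion; a baseline-adjusted comparison of scores would be more sensitive at almost no cost

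*Protocol article*

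**What the plan says.** Section 1.1 (Aims) of the protocol article places quality of life among the outcomes whose change is of interest: "Secondary aims of the study relate to changes in seizure frequency, retention on ketogenic diet therapy, adverse events related to dietary therapy, quality of life".

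Section 2.7.6 says that the NDDI-E and BrEASI "questionnaires will be completed at baseline (Week −2), at the completion of the treatment period (Week 14", and again at follow-up. Section 2.7.7 schedules the EQ-5D-5L and QOLIE-31 at baseline, Week 14 and follow-up: "Health‐related QOL will be measured by both generic and epilepsy‐specific instruments".

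Section 3.3 then fixes how these scales are compared at the end of the 12-week treatment phase: "The proportion of participants experiencing a clinically meaningful improvement in psychiatric symptoms and QOL questionnaire scores will be compared between groups".

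Two other uses of the same information are stated. The primary e-DOOR in section 2.4 has "three levels of quality of life, resulting in 60 combinations of potential outcomes"; Table 2 names the three levels as improvement, no change and worsening. For the EQ-5D-5L, section 2.7.9 says that "a preference‐based scoring algorithm will be used to generate scores" for the economic evaluation. Section 3.4 leaves the full analysis details to the statistical analysis plan.

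**The concern.** Four scored scales, each measured before and after treatment, are reduced to improved or not improved. Three things follow.

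- **Size of change.** A change just above the threshold counts the same as a very large one, and a change just below it counts the same as none.
- **Precision.** Baseline enters only through the definition of a responder. The gain from using the baseline score as a covariate for the Week 14 score is not taken.
- **Worsening.** Within a participant, a clear deterioration is scored like no change. For quality of life the e-DOOR keeps that distinction. NDDI-E and BrEASI are not components of the e-DOOR, so no stated endpoint separately counts worsening on them.

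At stake is the stand-alone reading of quality of life, which is one of the three e-DOOR components, and of mood. A real, moderate benefit could easily be reported as no clear difference.

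This is not a matter of detail left to the analysis plan. Section 3.3 defines the endpoint itself, and an analysis plan that follows it would analyse a proportion.

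**Working it through.** **Sample size.** Section 3.1 states: "Recruiting 108 participants would provide a power of 0.8 to detect the hypothesized treatment effect". With win/draw/loss of 0.6/0.1/0.3 and win ratio 2, the usual win-ratio formula is

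N = 4(1 + p_tie) / [3k(1 − k)(1 − p_tie)] × (z_α/2 + z_β)² / (ln WR)².

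With k = 0.5, p_tie = 0.1, two-sided alpha 0.05 and 80% power, this is (4.4/0.675) × 7.849/0.4805 = 106.5, or 108 as a round number for two equal arms. At the printed alpha of 0.0533 it is 104.4. Also 108/0.8 = 135, or 136 for equal arms. The plan's figures reproduce, giving 54 evaluable per arm, or 68 with no losses. No power is stated for the quality of life and mood endpoints.

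**Assumed inputs.** None of these is in the document. Scores are normal with SD 1. Baseline to Week 14 correlation ρ is 0.5 or 0.7. The true between-arm effect d is 0.4 or 0.5 SD. A responder improves by at least 0.5 SD. Mean improvement in controls, m, is 0 or 0.2 SD. Tests are two-sided at 0.05.

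**Formulas.**
- ANCOVA: power = Φ(d / [√(1 − ρ²) × √(2/n)] − 1.96).
- Responder: the SD of change is s = √(2(1 − ρ)); p0 = 1 − Φ((0.5 − m)/s); p1 = 1 − Φ((0.5 − m − d)/s); then the pooled two-proportion test.

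**One case in full** (ρ = 0.5, d = 0.5, m = 0.2, 54 per arm).
- ANCOVA: standard error 0.866 × √(2/54) = 0.1667; 0.5/0.1667 − 1.96 = 1.04; power 0.85.
- Unadjusted change score: s = 1; power 0.74.
- Responder: p0 = 1 − Φ(0.3) = 0.382; p1 = 1 − Φ(−0.2) = 0.579. The standard error is 0.0962 under the null and 0.0943 under the alternative. (0.197 − 1.96 × 0.0962)/0.0943 = 0.09; power 0.54.

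The total loss is 31 points: about 11 from not adjusting and about 20 from dichotomising.

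**All cells at 54 per arm.**

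| ρ | d | ANCOVA | Responder, m = 0 | Responder, m = 0.2 | Loss (points) |
|---|---|---|---|---|---|
| 0.5 | 0.4 | 0.67 | 0.37 | 0.38 | 30 to 31 |
| 0.5 | 0.5 | 0.85 | 0.53 | 0.54 | 31 to 32 |
| 0.7 | 0.4 | 0.83 | 0.54 | 0.56 | 27 to 29 |
| 0.7 | 0.5 | 0.95 | 0.74 | 0.76 | 20 to 22 |

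At 68 per arm the same cells give a loss of about 14 to 33 points.

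**In participants** (ρ = 0.5, d = 0.5, m = 0, 80% power). ANCOVA needs about 2 × 7.849 × 0.75/0.25 = 47 per arm. The responder comparison, 30.9% against 50.0%, needs about 102 per arm.

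**Sensitivity.** Over a wider grid (ρ 0.3 to 0.8, d 0.3 to 0.6, control responder rate 10 to 50%, 54 or 68 per arm) the loss runs from 1 to 52 points. It almost vanishes when effect and correlation are both high: with ρ = 0.8, d = 0.6, control rate 30% and 68 per arm, both powers exceed 0.99. In a simulated mood scale with half the participants starting at the symptom-free end, at 54 per arm, the loss is roughly 34 to 53 points, because those participants cannot improve in either arm. Table 1 sets no entry criterion on mood, so that fraction is unknown.

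**Sensitivity to harm.** With ρ = 0.5 and m = 0, a 0.5 SD worsening under the intervention lowers its responder rate from 30.9% to 15.9%; power to detect this is 0.45 at 54 per arm. With ρ = 0.7 and m = 0.2 it is 0.67. ANCOVA has 0.85 and 0.95 in the same two cases.

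**The case against.** The strongest reply is that this is a design preference on a secondary endpoint. Section 3.1 powers only the win ratio. A proportion with meaningful improvement is easy to explain to patients and matches the 50% seizure-reduction endpoint in the same section. An aim concerning change in quality of life is compatible with a responder defined on change. The unseen analysis plan may fit an adjusted model to the proportion or add mean-score analyses. All of this stands, and it means that no figure is wrong and no passages contradict each other. It does not remove the point, because section 3.3 fixes the improvement proportion as the comparison while the scores for a more sensitive one are already collected.

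Three stronger readings are tempting, and the document does not support them.

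- **That baseline scores are discarded.** Improvement is measured from baseline, so baseline defines the responder. What is lost is its use as a covariate and the size of the change.
- **That worsening cannot show at all.** A harmful effect lowers the intervention arm's responder proportion, with power of about 0.45 to 0.67 in the cases above. That is insensitive, not blind. The e-DOOR also has a worsening level for quality of life, and adverse events related to dietary therapy are compared by number and severity. The remaining gap is a separate count of worsening on NDDI-E and BrEASI.
- **That a loss as high as 53 points can be attached to the trial.** That figure needs half the participants at the symptom-free end, which nothing in the document supports, and it would concern the mood scales, not QOLIE-31 or EQ-5D-5L.

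**Conclusion.** The point holds as an efficiency improvement to a secondary endpoint. Section 3.3 reduces four scored scales to an improvement-only proportion. This loses the size of change and the precision from adjustment, and within a participant merges worsening with no change. At 54 per arm, with a 0.5 SD threshold, correlation 0.5 to 0.7 and an effect of 0.4 to 0.5 SD, the cost is about 20 to 32 points of power against ANCOVA. Everything in that statement except the sample size is assumed. The loss is smaller for large effects with high correlation, and reaches about 50 points on the mood scales only if many participants start at the symptom-free end. The primary analysis and the sample size are unaffected. Label: cheap improvement.

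**What to change.** In section 3.3, make the comparison for each of NDDI-E, BrEASI, QOLIE-31 and EQ-5D-5L the between-arm difference in mean Week 14 score, adjusted for the baseline score and the two stratification factors in section 2.5 (seizure frequency, and need for a medical treatment decision maker or caregiver), with a 95% confidence interval. Keep the proportion with clinically meaningful improvement as a supportive result, and report the proportion with meaningful worsening beside it, in line with the three quality of life levels of the e-DOOR.

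The cost is a change of wording in section 3.3 and in the analysis plan. No new data, visits or participants are needed. The one small downside is that a score difference is less directly meaningful to lay readers, so the two proportions should be shown next to it.
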